**Figure 1 F1:**
[figure not shown]
**Flowchart of the protocol steps**.

The patients allocated to the intervention group receive the treatment for 12 weeks, twice a week, 40-60 min per session. They are assessed at baseline condition (A1), after 12 weeks (A2-intervention period), and after 24 weeks (A3-follow-up period).

The patients allocated to the control group represent the crossover arm of the study. They also are assessed at baseline condition (A1) and after 12 weeks (A2). During this period, they continue to receive the usual recommended medical care at the hospital, which includes pharmacological treatment and self-care instructions. After the end of the second evaluation, they receive physiotherapy intervention for 12 weeks and are then assessed after intervention (A2'-24 weeks after baseline) and after the follow-up period (A3'-36 weeks after baseline). This design was chosen in order to increase the number of patients receiving the intervention, as we can expect losses to the follow-up evaluation due to the longer period of time required to complete all the protocol procedures (intervention and follow-up period).

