### Sample size and statistical analysis

The sample size calculation was made using an effect size of 0.36 (moderate effect size), considering the primary outcome measure of peak plantar pressure. We took the SD estimates from a study we completed, wherein we recruited a similar patient cohort [71]. A sample size of 46 subjects is needed to provide 81% power to detect a moderate effect difference between the highest and lowest group pressure means, assuming an alpha level of 0.05 and an statistical design of F test of repeated measures (between and within effects), and assuming a 10% loss to follow-up. The statistical analysis will be based on intention-to-treat analysis, and general linear models of analysis of variance for repeated measure will be used to detect treatment-time interactions. The outcome measures will be compared among baseline, 12 weeks, and 24 weeks. Cross-correlation analysis will also be provided between primary and secondary variables if it shows any relevance.

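### The planned three-visit treatment-by-time test includes a 24-week visit at which both arms have been treated; only the 12-week contrast compares the therapy with usual care

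*Protocol article*

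**What the plan says.** The design is in the protocol article under Overview of research design, in the text with Figure 1. The intervention arm is treated in weeks 0 to 12 and assessed at baseline (A1), week 12 (A2) and week 24 (A3). Of the controls it says "The patients allocated to the control group represent the crossover arm of the study". Up to week 12, "During this period, they continue to receive the usual recommended medical care at the hospital". After the week-12 assessment, "they receive physiotherapy intervention for 12 weeks and are then assessed after intervention". That assessment (A2') falls 24 weeks after baseline, and a further one (A3') follows at 36 weeks. The reason given is "This design was chosen in order to increase the number of patients receiving the intervention", in view of expected losses to follow-up.

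The analysis is under Sample size and statistical analysis. It is by intention to treat, and "general linear models of analysis of variance for repeated measure will be used to detect treatment-time interactions". The visits are then fixed: "The outcome measures will be compared among baseline, 12 weeks, and 24 weeks". This section does not mention the crossover and does not single out the 12-week contrast.

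**The concern.** The article states the model, the effect to be tested and the visits, and these conflict with the treatment schedule it also states. Up to week 12 the arms differ as treated versus usual care. By week 24 both have had the full intervention, at different times. The 24-week difference is therefore the effect retained in the early arm minus the fresh effect in the delayed arm.

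An interaction over all three visits mixes the 12-week effect, its persistence in the early arm and the controls' own response. A significant result would not show which of these produced it. Persistence matters here: the Hypotheses section notes that retention had not been studied beyond ten days, and the Background criticises earlier studies for short or absent retention follow-up.

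**Working it through.** **1. Treatment status at each visit in the planned test**

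| Visit | Intervention arm | Control arm | Between-arm contrast |
|---|---|---|---|
| Baseline | untreated | untreated | none expected |
| Week 12 | just treated (A2) | usual care only (A2) | therapy versus usual care |
| Week 24 | 12 weeks after treatment (A3) | just treated (A2') | early versus delayed treatment |

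**2. The plan's own sample size.** Stated inputs: effect size 0.36, alpha 0.05, 46 subjects, 81% power, 10% loss. Assumed: 0.36 is Cohen's f, two groups, m = 3 visits. For the interaction F test with 2 and 2(N−2) degrees of freedom, noncentrality = f²(N−2)(m−1).
- N = 41: 0.1296 × 39 × 2 = 10.11, power 80.4%.
- N = 41.4 (46 × 0.9): power 80.8%.
- N = 42: power 81.5%.
- 41/0.9 = 45.6, rounded up to 46.

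The stated figure is reproduced as a three-visit interaction test.

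**3. Expected between-arm differences.** Let d be the effect at the end of treatment and r the share retained 12 weeks later, and let controls gain the same d once treated. The differences at 0, 12 and 24 weeks are 0, d and rd − d = −(1−r)d. With d = 2 × 0.36 = 0.72 SD:
- full retention (r = 1): 0 / 0.72 / 0
- half retention (r = 0.5): 0 / 0.72 / −0.36
- no retention (r = 0): 0 / 0.72 / −0.72

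Full retention here gives the same 0 / 0.72 / 0 as an effect that vanished against controls left untreated. The 12-week difference is 0.72 in every case.

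**4. Power of the three-visit interaction.** With N = 41 completers in equal arms and compound symmetry with correlation ρ, noncentrality = (N/4) × S/(1−ρ), where S is the sum of squared deviations of the three differences from their mean. S = 0.3456, 0.6048 and 1.0368 for r = 1, 0.5 and 0. At ρ = 0.5 the noncentralities are 10.25 × S/0.5 = 7.08, 12.40 and 21.25.

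| ρ (assumed) | r = 1 | r = 0.5 | r = 0 |
|---|---|---|---|
| 0.3 | 49% | 75% | 94% |
| 0.5 | 64% | 88% | 99% |
| 0.7 | 86% | 98% | about 100% |

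Power rises as retention falls, at every correlation tried. These values differ from 81% because step 2 applies f to the interaction directly, while this step places 0.72 SD at week 12. That gap is not itself an error in the plan.

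**5. Power of the 12-week contrast adjusted for baseline.** Noncentrality = (N/4)d²/(1−ρ²), with 1 and N−3 degrees of freedom; 10.25 × 0.5184 = 5.31.
- ρ = 0.3: 5.31/0.91 = 5.84, power about 65%.
- ρ = 0.5: 5.31/0.75 = 7.08, power about 74%.
- ρ = 0.7: 5.31/0.51 = 10.42, power about 88%.

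**The case against.** The strongest reply is that the model contains what is needed. The baseline-to-12-week contrast is randomised, uncontaminated and estimable within the planned analysis. A reader might infer from the crossover that the trial cannot estimate the treatment effect; the documents do not support that.

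A reader might also infer that the plan would take convergence at 24 weeks as loss of effect. The article states no such rule. It lists time points and does not say what conclusion a 24-week difference would carry.

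Third, the 24-week comparison of early with delayed treatment is still randomised and has a meaning. If controls gain the same d, r can even be recovered as 1 + (24-week difference)/d. This stands, but it rests on that equal-gain assumption, and no untreated group is left at 24 weeks to check it.

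Fourth, the paired labels A2/A2' and A3/A3' suggest that alignment by treatment phase may be intended, and an article may leave the use of the 36-week visit to the analysis plan. That is fair, so the absence of A3' from the stated analysis is not counted here. It is also true that the article promises no controlled estimate of retention.

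What survives is narrower. The test the article states is the interaction across all three visits, and no contrast is named that would keep the 24-week visit out of the efficacy conclusion.

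**Conclusion.** The point holds for the omnibus interaction and for the 24-week contrast. Neither estimates the effect against usual care or retention against untreated controls. It does not extend to the trial as a whole, because the 12-week comparison is sound.

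The direction of the problem follows from the schedule, given that controls respond to treatment as the intervention arm does. Its size depends on reading 0.36 as Cohen's f, 41 completers, compound symmetry and a correlation that the article does not give. Across correlations of 0.3 to 0.7, interaction power is 49% to 86% if the whole effect lasts and 94% to about 100% if none of it does. A significant interaction is thus some evidence that the arms' courses differ, but it cannot be read as lasting benefit.

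**What to change.** - Name the between-arm difference at 12 weeks, adjusted for baseline, as the confirmatory comparison, and do not use the three-visit interaction as the test of efficacy.
- Label any 24-week between-arm difference as early versus delayed treatment.
- Report retention as within-arm change, A2 to A3 in the intervention arm and A2' to A3' in the control arm, and say that it has no untreated control.

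No visits or data are added. The cost lies in the power statement: 81% belongs to the three-visit interaction and must be restated for the 12-week contrast. Under the assumptions above it is about 65%, 74% or 88% at correlations of 0.3, 0.5 and 0.7, so the sponsor should state the correlation it expects and may find that 46 patients give less than the power claimed.

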### Hypotheses

The literature update shows that, with ROM exercises and gait training, individuals with DPN can improve their confidence and balance, and they can change plantar pressure distribution during gait, although retention of these interventions was not studied for more than ten days. There is still a gap in the literature regarding whether a specific training for improving foot rollover and redistributing plantar pressure during gait could be effective in predicting risk of ulceration over a long-term period. If we look at some of the interventions applied to this population, general lower limb exercises of the ankle, knee, and hip are recommended, without training the small foot joints, which play an important role in foot rollover and load absorption during locomotion. Conversely, other studies only applied segmental exercises, without training foot rollover during gait. None of the therapies cited were able to integrate the peripheral gains (muscle strength and ROM improvements) to foot function during daily locomotor tasks.

Considering the possibility of recovering some foot and ankle function, foot rollover could also be improved, and consequently, the risk of foot ulceration could be reduced. This approach is quite new, as the standard treatment has focused on plantar load relief by introducing orthotic devices and insoles that passively change the plantar pressure distribution, without exploring the possibility of improving function. That is, this new intervention focuses on recovering the causes of movement abnormalities, intending a redistribution of plantar pressure during gait through an active intervention. Although some of the impairments are permanent, such as sensitivity loss, recent evidence leads us to believe that it is possible to attain some recovery.

A well-designed therapeutic exercise protocol, including interventions aimed at joint, muscle, and locomotor task recovery, should be part of a physical therapy routine prescription. Although this comprehensive approach is imperative in clinical practice, its functional and biomechanical effects have not yet been tested. Most importantly, if effective, these exercises might be performed by the patient without needing physiotherapy supervision, representing a way of reducing costs associated with diabetic patients' treatment.

Our hypotheses are:

(I) The specific training proposed could improve muscle function and foot and ankle ROM.

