(II) It could be reflected in the foot rollover during gait, improving plantar pressure distribution and lower limb kinematics.

Therefore, our aim is to investigate the effect of exercise therapy intervention on foot rollover during gait, ROM, and muscle strength and function of the foot and ankle complex, as well as balance confidence when performing walking tasks.

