### Biomechanical assessment

Plantar pressure is recorded using the Pedar-X system (Novel, Munich, Germany) at 100 Hz. The patient walks barefoot on a 10 m flat walkway at a self-selected cadence (controlled between subject's trials within 96-116 steps/min), with the insole placed and fixed, using an anti-skid sock and a stripe at the ankle. Four valid trials are recorded, and we discard the first and last steps from the analysis. The foot is divided into six areas (heel, midfoot, lateral forefoot, middle forefoot, medial forefoot, hallux, and toes), using the same software for data acquisition. A time-series analysis will be performed to compare the pressure curve in each area, over the stance duration, intending to describe changes in plantar pressure distribution. Values of contact area and peak pressure will be compared in these six areas.

Kinematic gait parameters are acquired using three-dimensional displacement of passive reflective markers (20 mm in diameter) tracked with six infrared cameras (OptiTrack FLEX: V100, Natural Point, Corvallis, OR, USA) (Trombini-Souza et al., 2011). The markers are placed on the subject using a standard Cleveland Clinic marker set (iliac spine antero-superior, superior aspect of the greater trochanter, lateral knee joint line, lateral malleolus, calcaneus, and head of the fifth metatarsal) [70]. Extra markers are placed bilaterally at the medial knee joint line, medial malleolus, and first metatarsal joint for the static standing trial, in order to determine relative joint centres of rotation for the knee, ankle, and longitudinal axis of the foot. These extra markers are removed in the gait trial. In addition, three non-collinear reflective markers are fixed at two squares, forming sets of technique cluster. One of these is placed in the lateral thigh and the other over the shank. Theses landmarks are determined by the same physiotherapist who performs the blind assessment. The laboratory coordinate system is established at one corner of the force plate, and all initial calculations are based on this coordinate system. Each lower limb segment (foot, shank, and thigh), based on surface markers, is modelled as a rigid body with a local coordinate system that coincides with the anatomical axes, and translations and rotations of each segment are reported relative to neutral positions defined during the initial standing static trial.

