Ground reaction forces are acquired by a force plate (AMTI OR-6-1000, Watertown, MA, USA) embedded in the centre of the walkway.

Force and kinematic data acquisition are synchronized and sampled by an A/D card (AMTI, DT 3002, 12 bits) at 100 Hz. Mathematical analysis of the kinematic data will be performed using Visual3D software (C-motion, Kingston, ON, Canada), and the ground reaction force analysis will be performed using a custom-written Matlab function (MathWorks, Natick, MA, USA). The variables to be analysed are: (1) joint angles and (2) net ankle moments in the sagittal and frontal planes; and (3) step length and (4) duration. These variables will contribute to discussion of the possible changes in plantar pressure distribution, especially the ankle position in the initial and terminal stance phases.

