### Outcome measures

The main outcome measure is foot rollover, which will be described by time-series analysis of plantar pressure distribution during gait. This variable was chosen because it reflects the alterations of kinematics, kinetics, and muscle function in the dynamic task of gait.

The secondary outcomes are foot and ankle kinetics and kinematics during gait, neuropathy signs and symptoms, foot and ankle ROM, function and muscle strength, and Activities-Specific Balance Confidence Scale [67].

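### Reporting of the supplementary cross-correlation between primary and secondary variables depends on its own result, which hides null associations and overstates those shown

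*Protocol article*

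**What the plan says.** The rule is the last sentence of the Protocol article's section Sample size and statistical analysis: "Cross-correlation analysis will also be provided between primary and secondary variables if it shows any relevance". No criterion for relevance is attached to it.

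The same section gives the main method, with no such condition: "general linear models of analysis of variance for repeated measure will be used to detect treatment-time interactions".

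The Hypotheses section sets out a two-step argument. The first step is "The specific training proposed could improve muscle function and foot and ankle ROM"; the second is "It could be reflected in the foot rollover during gait, improving plantar pressure distribution and lower limb kinematics". Under Outcome measures the primary variable is a curve, not a single number: "The main outcome measure is foot rollover, which will be described by time-series analysis of plantar pressure distribution during gait". The secondary variables are broad: "The secondary outcomes are foot and ankle kinetics and kinematics during gait, neuropathy signs and symptoms, foot and ankle ROM, function and muscle strength", and the balance confidence scale completes the list. Biomechanical assessment adds scalar pressure measures by region, "Values of contact area and peak pressure will be compared in these six areas", and says of the gait variables: "These variables will contribute to discussion of the possible changes in plantar pressure distribution".

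**The concern.** The sentence makes publication of an analysis conditional on its outcome. This is a rule the article states, not a detail left for an analysis plan. A fuller plan could define relevance, but reporting would still follow the result unless the condition were removed.

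The rule falls on a link that matters to the trial's rationale. The argument is that gains in range of motion and muscle function carry over to foot rollover. The repeated-measures models test the effect of treatment on each outcome in turn. They do not ask whether patients who gain more range of motion or strength also change their plantar pressure more. Only the cross-correlation addresses that question directly. If it is shown only when it looks relevant, readers cannot tell a supported association from one that survived selection, and associations near zero go unseen.

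**Working it through.** The article states no figure for these correlations, so there is nothing of its own to reproduce. The steps below size the effect of the rule under labelled assumptions.

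**Inputs from the article.** 46 patients, 10% loss and alpha 0.05 (Sample size and statistical analysis). 46 × 0.90 = 41.4, so 41 to 46 patients contribute. Six plantar regions are stated, although the list in the same paragraph of Biomechanical assessment names seven. Seven secondary families can be counted under Outcome measures: kinetics, kinematics, neuropathy signs and symptoms, range of motion, function, strength and balance confidence.

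**Assumptions not in the article.** Relevance means two-sided p<0.05. The statistic is a between-patient Pearson r. The filter acts on each pair separately. The number of pairs is 6 regions × 7 families = 42, or 7 regions × 10 secondary variables = 70, where the 10 is assumed.

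**Step 1: smallest correlation that would be shown.** r_crit = t / √(n − 2 + t²), with t the 97.5% point on n − 2 degrees of freedom.
- n = 46: 2.0154 / √(44 + 4.0618) = 0.291
- n = 41: 2.0227 / √(39 + 4.0913) = 0.308

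**Step 2: chance that a true r of 0.20 is shown (Fisher z approximation).** P ≈ P(Z > [atanh(r_crit) − atanh(0.20)] × √(n − 3)).
- n = 46: (0.2997 − 0.2027) × √43 = 0.636, so P ≈ 0.26
- n = 41: (0.3183 − 0.2027) × √38 = 0.713, so P ≈ 0.24

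Simulation of bivariate normal samples (1,000,000 per setting) gives 0.267 and 0.242.

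**Step 3: average correlation among those shown (same simulation).**

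| True r | n | Proportion shown | Mean when shown |
|---|---|---|---|
| 0 | 46 / 41 | 0.05 / 0.05 | absolute value 0.34 / 0.36 |
| 0.20 | 46 / 41 | 0.27 / 0.24 | 0.37 / 0.39 |
| 0.30 | 46 / 41 | 0.54 / 0.49 | 0.40 / 0.42 |

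A true 0.20 is therefore reported at 0.37/0.20 = 1.85 to 0.39/0.20 = 1.95 times its size.

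**Step 4: null pairs that pass.** The expected number is 0.05 × K: 0.05 × 42 = 2.1 and 0.05 × 70 = 3.5. For 42 independent null pairs, the chance of at least one is 1 − 0.95^42 = 0.88. Correlation among the pairs would lower that 0.88 but would change neither the expected count nor the inflation in Step 3.

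**The case against.** The strongest reply has four parts.

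1. **The analysis is supplementary.** A reader might infer that the trial's evidence for its hypotheses is selected on its own result. The article does not support that. Improvement in range of motion and muscle function, and change in plantar pressure and kinematics, are each assessed by a randomised comparison that is reported without condition. If strength or range of motion does not improve, that comparison will show it. The article also commits the gait variables to interpreting pressure changes without any filter, and nowhere says that a mechanism will be claimed from the correlations. This part stands and limits the weight of the point.

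2. **The statistic may be a different one.** Cross-correlation is also the name of a method for comparing two time curves, and both the main outcome and the joint angles and moments are curves. If that is meant, the thresholds and inflation figures above do not apply. The article does not settle it, so the arithmetic is an illustration only.

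3. **Filtering pair by pair is one reading.** A reader might infer that the plan necessarily yields a filtered list of pairs. The condition can equally refer to the analysis as a whole. Null pairs would then still appear whenever the analysis is provided, and the per-pair inflation would not follow. On either reading, a wholly null analysis may go unreported.

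4. **Relevance could mean clinical or scientific interest, and the list of pairs may sit in an analysis plan.** Both are fair. The missing list, time point and coefficient are not the complaint. But tying provision to what the analysis shows remains result-dependent whatever relevance means.

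**Conclusion.** The point holds at low severity. The stated rule makes reporting of one supplementary analysis depend on its result, and that analysis is the only named one directly relating foot and ankle gains to plantar pressure. Following it would suppress null associations and tend to overstate those reported. The primary treatment comparison, the alpha level and the sample size do not change.

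That conclusion rests on the wording alone. Its size does not: the near doubling of a true correlation of 0.20, and the 2 to 3.5 chance findings, require all the assumptions listed in the working and should not be read as what the plan will produce.

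**What to change.** Delete the closing condition from the sentence and replace it with a commitment along these lines: cross-correlations between the plantar pressure measures and the secondary variables, for a set of pairs fixed before unblinding, will all be reported with 95% intervals whatever the result, and are exploratory. The list of pairs can sit in the analysis plan. Saying whether curves or patient-level values are correlated would remove the ambiguity noted above.

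Where patients from both groups are pooled, adjust for arm. Otherwise a treatment effect on both variables would by itself produce a correlation, even if the two were unrelated among patients within each arm.

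The cost is one revised sentence and one supplementary table. No new data are needed, and the sample size, alpha level and main analysis stay as they are.
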